# **Inguinal hernia surgery in Sierra Leone; an implementation study of low cost anterior mesh repair performed by medical doctors and non-physician clinicians**

## **1. Introduction**

### ***Global surgery***

Five billion people do not have access to quality surgical services worldwide.(1) The unmet need for surgery is largest in sub-Saharan Africa (SSA) and South Asia.(2) Previously, surgery has been thought to be too resource intensive to be prioritised in poor countries, but simple surgical procedures are recently demonstrated very cost-effective.(3,4) Surgical conditions account for 28-32% of the global burden of disease, but have only recently been understood to be of public health significance.(2,5) The opportunities for research and work to improve surgical service delivery in low-income countries are extensive and much needed.

Global surgery is a field of study, research, practice and advocacy. Its aim is to achieve equity in surgical service delivery for all people worldwide.(6) Conditions like inguinal hernia, that result in a significant burden of disease, can only be successfully treated by surgery.(7) Surgical service provision requires functioning health care systems and infrastructure. Therefore, focusing on a condition like inguinal hernia that is treatable at first level hospitals has the potential to improve the delivery of surgical care in particular, but also act as an enabler for hospital health system strengthening in general.(8)

### ***Inguinal hernia – epidemiology and mosquito nets***

Inguinal hernia is a common surgical condition with an estimated 20 million hernia cases repaired every year worldwide,(9) and it is one of the most commonly performed surgical procedures in sub-Saharan Africa.(10,11)

However, 200 million patients living with inguinal hernia do not receive necessary surgical care. In Uganda where the annual hernia repair rate is 17 per 100,000 people, the met need for inguinal hernia surgery is less than 1% per year.(12)

In a systematic review the minimum total need for hernia repair in sub-Saharan Africa was 204 per 100,000, of which 175 per 100,000 were unmet.(13) The high number of inguinal hernias in Sub-Saharan Africa that go unrepaired results in a higher number of complications. In a study in East Africa, over 175 in 100,000 needed surgery for inguinal hernia and there were 30 strangulated hernia per 100,000 each year.(14)

Using mesh to achieve a tension-free inguinal hernia repair significantly reduces the risk of hernia recurrence and has been the preferred method in high-income countries for decades.(15) However, in resource constrained settings, most inguinal hernias are repaired using tissue techniques, which has significantly poorer outcomes compared to tension free mesh techniques. A commercial mesh costs over US\$100 and more than doubles the cost of a hernia repair in Uganda.(16) The cost of a commercial mesh in Sierra Leone is also around US\$100. A recently published double-blinded, randomized clinical trial carried out in Uganda shows that a mosquito net, which comes at a fraction of the cost of a commercial net, is a safe and effective alternative for elective inguinal hernia repair.(17) Mosquito net costs \$0.01, and the cost of sterilization is \$1.46.(18) In order to prove benefit for patients living in low-resource settings, this finding needs to be translated into practice.

### ***Task-shifting***

Task-shifting with non-surgeons is practiced in many African countries, depending on national policies .(19) The World Health Organisation (WHO) defines task-shifting as “the rational redistribution of tasks among health workforce teams from highly qualified workers to health workers with shorter training and fewer qualifications.”(20) In sub-Saharan Africa, non-surgeon physicians and Non-Physician Clinicians (NPCs) commonly perform inguinal hernia repair. NPCs are mid-level health care providers who receive training to perform duties that medical doctors would normally do. In this case, they are trained to undertake a selected number of surgical procedures. Though there is some data to support the safety of inguinal hernia repair by NPCs in Tanzania, further research is needed to support this practice for mesh repair.(21) NPCs in Sierra Leone are called Community Health Officers (CHOs), and some of them perform surgical procedures. According to recent data collected as part of the post-Ebola recovery process in March 2016 there are 648 CHOs in Sierra Leone.(22)

A nationwide inventory of surgical procedures and providers carried out in Sierra Leone in 2012 showed that there were 164 surgical providers. Of these, 14 (8.4%) were CHOs and they carried out 6.8% of the total national volume of surgery.(23)

### ***Sierra Leone***

Sierra Leone is a small country in West Africa, with an estimated population of just above 6.3 million people.(24) The country has been badly affected by a 10-year civil war between 1992 and 2002 and more recently experienced a devastating outbreak of Ebola.

In 2008 there were only 10 qualified surgeons catering for the whole of the Sierra Leonean population.(25) The Ebola outbreak has had a further impact on numbers of qualified doctors, as 11 out of the country’s 125 clinically practicing medical doctors died during the outbreak .(26) The shortage of doctors correlates with a huge unmet need for healthcare in general and surgery in particular. The unmet need for surgery in Sierra Leone has recently been documented to be 92.1%.(27) However, this calculation was done prior to the Ebola outbreak and the unmet need is likely higher now.

In 2012, 22.4% of all surgeries performed in Sierra Leone were hernia repairs. The prevalence of inguinal hernias in Sierra Leone has been estimated to be about 7%, while Ghana and Tanzania have documented prevalence’s of 10.8% and 12%, respectively .(28)(29)(30) Thus, the actual prevalence of inguinal hernia in Sierra Leone is likely to be in the range between 7 -12%.

Since 2011, CapaCare, a Norwegian NGO, has been collaborating with the Ministry of Health and Sanitation and the United Nations Population Fund in Sierra Leone to provide a Surgical Training Programme for non-surgeon doctors and CHOs. As of May 2016, the programme has trained 9 clinicians and another 26 are currently in training. The CHOs that complete the training are called Surgical Assistant CHOs. Second after caesarean sections, inguinal hernia repair is the most commonly performed surgical procedure by the trainees and the graduates of the programme. (31)

### ***Financial burden***

Sierra Leone ranks as 181 in the UN Human Development Index and 56.6% of the population live below the income poverty line (less than \$1.25 per day).(32)

Healthcare for pregnant, lactating women and children under 5 has been delivered free since 2010 in Sierra Leone. Besides free treatment for HIV, TB and Malaria, all other healthcare costs are paid by the patient, which is considered the main barrier to access healthcare.(33) Catastrophic health expenditure is defined in relation to a household's capacity to pay and occurs when the health costs exceed 40% of the total household expenditure.(34)(35)

Hernia repair in Sierra Leone costs between US\$ 50-75 and represents a vast financial burden that forces many into catastrophic health expenditure. Patients with hernias may also experience disability and potential loss of earnings. A 2013 cluster survey from Sierra Leone recorded that 20% of patients were unable to work due to their untreated hernias.(28) Furthermore, delay in seeking treatment for hernia is associated with higher morbidity and mortality and higher cost of emergency surgery in the event of strangulation.(36)

This project based in Sierra Leone will investigate how non-surgeon medical officers and surgical assistant CHOs can be trained to perform mesh hernia repair under local anaesthesia. The study will also compare outcomes between these two staff categories in order to detect any significant differences that will have to be taken into consideration for large-scale implementation of this hernia repair method in Sierra Leone and beyond. A cost-effectiveness analysis will also be undertaken. The Sierra Leone site contributes to a multicentre study on inguinal hernia repair in sub-Saharan Africa. It is part of a collaboration between multiple partnerships and builds on several years of research in African environments.(11,12,16,17)(23,26,27)

### **2.1 Benefit for patients and health services**

A low cost material can be used instead of an expensive mesh in groin hernia repair. To meet the vast need for surgery, task-shifting is an approach that is already practised in Sierra Leone.(23) However, the safety and effectiveness of this practice in groin hernia repair, specifically using a synthetic mesh has not been evaluated sufficiently. This study will do that and the results will be used to implement training initiatives, write national treatment guidelines and to inform policy makers, funders, NGOs and governments. The patients participating in the study will benefit directly as they will have their hernias repaired. The potential benefit for many millions of groin hernia patients living in resource scarce settings worldwide is considerable.

Integral to this study is the training of doctors and CHOs in mesh hernia repair, thereby directly improving standards in groin hernia repair. In addition, it is likely that this study will improve surgical quality and the function of the first level hospitals in general.

### **3. Topics and objectives**

The purpose of this project is to assess low cost mesh inguinal hernia repair in Sierra Leone. The specific aims are to:

1. Evaluate feasibility and effectiveness of implementation of inguinal hernia repair using low cost mesh
2. Assess whether non-physician clinicians and doctors can deliver comparable outcomes in inguinal hernia repair using low cost mesh.
3. Analyse cost-effectiveness of inguinal hernia mesh repair in Sierra Leone.

These aims will be addressed by a single blinded, randomized clinical trial.

## 4. Feasibility

The participants of this research team contribute with valuable and unique knowledge and experiences that ensure the feasibility of the project.

The PhD student, [name], is a Sierra Leonean medical doctor with experience from working in a variety of hospitals in Sierra Leone, with over 6 months at both of the study sites. He completed the CapaCare surgical training programme in 2013 and is currently undertaking postgraduate surgical residency training in Ghana with the West African College of Surgeons.

The Norwegian collaborators have extensive experience of clinical work and research, both previous and current in Sierra Leone. The Swedish collaborators, carried out a similar randomized clinical trial on groin hernia surgery in Uganda with follow up rates of over 95% one year postoperatively.(17)

### 4.1. Design, methodology and analysis

#### Theory

A low cost mosquito mesh can be used instead of an expensive commercial mesh to electively repair inguinal hernias in adult males.(17) An implementation study of the low cost mesh repair is necessary to guide the introduction of the technique on large scale in resource-constrained settings.

To increase access to surgical services, task-shifting with non-surgeons and NPCs is already practiced in several sub-Saharan African countries.(19) A study comparing these staff cadres is necessary to determine the safety and efficacy of task-shifting of mosquito net mesh repair.

#### Method

**Study design:** Single-blinded, randomised clinical trial

**Study population:** The project will be undertaken in two hospitals in northern Sierra Leone – Kamakwie Wesleyan Hospital and Masanga Hospital, both longstanding partner hospitals in CapaCare's Surgical Training Programme.

**Sample size calculation:** *Statistical rationale:* Based on a non inferiority design the assumptions are as follows: 80% power, 5% significance level, 5% non-inferiority limit and expected success rate of 98% in both arms results in a sample size of 97 individuals in each group. Correcting for an expected 15% loss to follow up we adjust the sample size to 114 in each group, or 228 in total.

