204 supervision, and practical test scores). Patient interviews including medical history,  
205 the EuroQol 5D (EQ5D) and the Inguinal Pain Questionnaire (IPQ) will be done  
206 preoperatively, at follow up two weeks and one year after surgery. Physical  
207 examination will be undertaken preoperatively in conjunction with the interviews to  
208 verify that the patients meet the inclusion criteria, and also at two weeks and one year  
209 postoperatively in order to detect post operative complications and recurrences.  
210 Expenses associated with the training and the surgeries will be recorded.

211 ***Data analysis:*** Surgical trainee data will be analysed descriptively. Primary endpoints  
212 for patient data include hernia recurrence. Secondary endpoints include postoperative  
213 complications, chronic pain and patient satisfaction. The outcomes following surgery  
214 performed by medical doctors and CHOs will be compared. Results from Sierra  
215 Leone will be compared with results from the other collaborating centres. When  
216 comparing data, two sample t-tests will be used for continuous variables and  
217 Pearson's Chi-square or Fisher exact test will be used for counts. A p-value < 0.05  
218 will be considered statistically significant.

219 Cost effectiveness will be expressed as USD per Disability Adjusted Life Year  
220 (DALY) averted and USD per Quality Adjusted Life Year (QALY) gained. The  
221 EuroQol questionnaire will be used to calculate QALYs gained (before surgery  
222 compared to one year postoperatively).(39) The Inguinal Pain Questionnaire results  
223 will be used to calculate DALYs gained (before surgery compared to one year  
224 postoperatively).(40)

225 The cost analysis will be done from the care provider's perspective. It will include  
226 staff time, material consumption in relation to the surgery as well as hospital overhead  
227 costs and capital costs.

228 Disability weights for the DALY calculation will be achieved by converting the  
229 results from the seven-level IPQ into the three-level disability weights for  
230 abdominopelvic as outlined in the Global Burden of Disease study 2010.(41) The  
231 disability weight one year after the surgery will be subtracted from the disability  
232 weight before the surgery. DALYs averted will be calculated by multiplying the  
233 disability weight difference with the remaining life expectancy of the patient

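### The 97 per group and 80% power hold only for an unstated one-sided 5% non-inferiority test, which the analysis rule of p < 0.05 on difference tests does not match; judged on a 95% interval, power is about 70%

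*Protocol*

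**What the plan says.** The sample size paragraph in section 4.1 (Method) opens with "Based on a non inferiority design the assumptions are as follows". It then gives "80% power, 5% significance level, 5% non-inferiority limit", with an "expected success rate of 98% in both arms", and concludes that this "results in a sample size of 97 individuals in each group". Allowing for 15% loss, it enrols 114 per group, 228 in total. Nothing in the paragraph says whether the "5% significance level" is one-sided or two-sided, and no confidence interval is mentioned.

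The Data analysis paragraph of the same section names hernia recurrence as a primary endpoint and says that outcomes of doctors and CHOs will be compared. For comparisons it lists two-sample t-tests for continuous variables and Pearson's chi-square or Fisher's exact test for counts. The threshold is "A p-value < 0.05", again without sidedness. The paragraph does not refer to the non-inferiority limit, to a confidence interval for the difference, or to a rule for concluding non-inferiority.

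**The concern.** The two paragraphs write the same figure, 5% or 0.05, but on their ordinary reading they stand for different error rates. The 5% behind the sample size has to be one-sided for 97 to come out. The p < 0.05 in the analysis belongs to tests that are normally two-sided, whose interval counterpart is a 95% confidence interval, or 2.5% on the side that matters for non-inferiority. In addition, the listed tests address the hypothesis of no difference. A non-significant chi-square or Fisher result does not show that the difference is below 5 percentage points.

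The second aim is to find out whether the two cadres deliver comparable outcomes, and the results are meant to inform national policy on training CHOs. A result whose upper limit lies under 5 points on a 90% interval and over it on a 95% interval would be read both ways, and the protocol does not settle which reading counts. If the level is settled only once the data are known, it will look selected.

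**Working it through.** **Inputs, all from the sample size paragraph:** success 98% in both arms, so the true difference is 0; limit 5%, taken as 5 percentage points absolute; power 80%; 97 evaluable per group; 15% loss.

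**Reproducing the protocol's figure.** The usual non-inferiority formula with unpooled variance is

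n = 2 × p(1 − p) × (z_α + z_β)² / d²,

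with 2 × 0.98 × 0.02 = 0.0392, d² = 0.0025 and z_β = 0.842.

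- One-sided 5% (z_α = 1.645): n = 0.0392 × 2.487² / 0.0025 = 96.9, so 97. This is the protocol's number.
- Loss to follow-up: 97 / 0.85 = 114.1, which agrees with 114 apart from rounding.

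**The same formula at one-sided 2.5%** (z_α = 1.960): n = 0.0392 × (1.960 + 0.842)² / 0.0025 = 123.07, so 124 per group. With loss, 124 / 0.85 = 145.9, so 146 per group, or 292 in total.

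**Other standard calculations do not give 97.** A score-type variance needs about 145 per group at one-sided 5% and 187 at 2.5%. Equivalence by two one-sided tests at 5% needs about 135. A superiority test of 98% against 93% needs 212 (one-sided) or 269 (two-sided). Of the variants tried, only one-sided 5% with the unpooled variance fits.

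**Power with 97 evaluable per group.** The standard error is √(0.0392 / 97) = 0.0201, and 0.05 / 0.0201 = 2.487.

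- One-sided 5%: Φ(2.487 − 1.645) = 80.0%.
- One-sided 2.5%: Φ(2.487 − 1.960) = 70.1%.
- One-sided 2.5% if all 114 per group were evaluable: 76.9%.

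**Exact check.** With failure rates of 2%, the normal approximation is rough. Enumerating all outcomes for 97 per group at a true rate of 98% in both arms gives:

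| Limit | One-sided 5% | One-sided 2.5% |
|---|---|---|
| Wald | 81% | 75% |
| Newcombe | 64% | 47% |

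Power falls with either method when the level moves to 2.5%, by about 6 points with Wald limits and about 16 with Newcombe limits.

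**How the level can decide the result (illustrative counts, not from the protocol).** Take 3 recurrences among 97 in one group and 2 among 97 in the other. The difference is 1.03 points. The standard error is √[(0.0309 × 0.9691 + 0.0206 × 0.9794) / 97] = 2.27 points. The Wald upper limit is 1.03 + 1.645 × 2.27 = 4.8 points on a 90% interval, and 1.03 + 1.960 × 2.27 = 5.5 points on a 95% interval. The first is inside the limit and the second is outside.

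**The case against.** The strongest reply is that nothing has been miscalculated. Non-inferiority is a one-sided hypothesis, so a one-sided 5% level is a literal reading of the sample size paragraph, and at that level both 97 and 80% are correct. This stands: a reader might infer an arithmetic error, and the document does not support one.

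The second reply is that the protocol never says two-sided. This also stands. A reader might take the analysis threshold to be a stated two-sided 5% and conclude that the two paragraphs contradict each other outright. Two-sidedness is only inferred from the tests named and from the absence of any one-sided test. The threshold also governs difference tests, including comparisons with other centres, so 70% is not the power of any rule that the protocol has adopted for non-inferiority. It is conditional on judging non-inferiority at one-sided 2.5%.

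The third concerns size. A reader might quote 47% as the true power. That figure combines the change of level with a change of interval method. Its proper comparator is 64% with the same Newcombe limit at one-sided 5%, not 80%.

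The last is that interval level and method are commonly left to the SAP, which is not at hand and may already fix a 90% interval. That is fair for the interval method. But the protocol itself fixes the error rate that justifies 228 patients, and its own analysis paragraph gives a decision rule that neither matches that rate nor tests the limit. Carrying out that paragraph as written would not deliver the comparison that was powered.

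**Conclusion.** The point holds as a mismatch between the design level and the analysis rule. The stated 80% power belongs to a one-sided 5% non-inferiority test that the protocol does not name. The only rule it does give is p < 0.05 on tests of no difference. If non-inferiority is judged on the conventional counterpart of that threshold, a 95% interval, power is about 70% by the formula that reproduces the protocol's figure, and 80% would take 124 evaluable per group (146 enrolled).

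This rests on four assumptions: the limit is absolute, success means freedom from recurrence (the sample size paragraph does not define it), both true rates are 98%, and 97 per group are evaluable. The size of the loss depends on the method, about 10 points by the normal approximation, 6 by exact Wald and 16 by exact Newcombe, but its direction does not. The matter should be corrected; it does not make the number of patients wrong for a one-sided 5% test.

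**What to change.** Either of two changes would do. Each takes about one sentence in the sample size paragraph and one in the Data analysis paragraph, and neither alters enrolment.

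1. State that recurrence is judged for non-inferiority at one-sided 5%, by comparing the upper limit of a two-sided 90% confidence interval for the difference in recurrence (CHOs minus doctors) with 5 percentage points. Confine the p < 0.05 difference tests to the other comparisons. The cost is an openly stated 5% one-sided error rate, which some readers will find lenient.
2. Judge recurrence on a two-sided 95% confidence interval, keep 228 patients, and restate the power as about 70% (normal approximation). The cost is a less favourable stated power.

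Under either option the interval method should be named before the data are seen, because the exact power depends on it.

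### The stated 80% power at a 5% level does not hold with 97 per group: with about two failures expected per arm, an interval that keeps its level gives about 64%

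*Protocol*

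**What the plan says.** The sample size paragraph in protocol section 4.1 (Method) sets up a non-inferiority comparison: "Based on a non inferiority design the assumptions are as follows". The inputs are "80% power, 5% significance level, 5% non-inferiority limit", and the result is that an "expected success rate of 98% in both arms results in a sample size of 97 individuals in each group". The allowance for attrition follows: "Correcting for an expected 15% loss to follow up", "we adjust the sample size to 114 in each group, or 228 in total".

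The paragraph gives no formula and no interval method, and does not say whether the 5% level is one- or two-sided. The data analysis paragraph says primary endpoints "for patient data include hernia recurrence", so success is read here as no recurrence. For counts it names Pearson's chi-square or Fisher's exact test, which as named are tests of equality and supply no non-inferiority limit.

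**The concern.** At 98% success, 97 patients yield 97 × 0.02 = 1.94 expected failures per arm. Normal-approximation formulas for a difference in proportions are unreliable at counts this low. The unpooled variance estimate is too small when few or no failures are seen, so the Wald upper limit falls too low and non-inferiority is declared too easily.

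If 97 was obtained that way, the 80% power is bought by exceeding the 5% level. Either the analysis uses a Wald limit and claims comparable outcomes too often, or it uses a limit that respects the level and fails too often when the two cadres are truly identical. Section 4.3 says the results are to influence national policy on hernia repair and on training, so both errors have consequences.

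**Working it through.** **Inputs.** All come from the sample size paragraph in section 4.1: power 80%, level 5%, margin 5% (taken as percentage points on the risk difference), success 98% in both arms, equal groups, 15% loss.

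**Reproducing the plan's figure.** Unpooled normal approximation:

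n per arm = (z₁₋α + z₁₋β)² × 2 × p(1−p) / margin²

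- One-sided 5%: (1.645 + 0.842)² × 2 × 0.98 × 0.02 / 0.05² = 96.9, so 97. This matches.
- One-sided 2.5%: the same formula gives 124. This does not match.
- Attrition: 97 / 0.85 = 114.1, against 114 stated.

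The plan's 97 is therefore this formula at one-sided 5%. That is inferred from the match, since the protocol does not say so.

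**Exact operating characteristics.** For each rule, list every pair of failure counts (CHO arm, doctor arm) for which the one-sided 95% upper limit for the difference in failure risk is below 0.05. Then sum the product of the two binomial probabilities over those pairs. Power uses 2% failures in both arms. Type I error uses 7% versus 2%, which is exactly at the margin. The worst case is taken over doctor-arm failure rates from 0 to about 10%.

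| Rule, 97 per arm, one-sided 5% | Power | Type I error, 7% vs 2% | Worst case |
|---|---|---|---|
| Wald (unpooled) | 80.7% | 7.75% | 13.1% |
| Agresti-Caffo | 71.3% | 5.05% | 5.5% |
| Wald, continuity-corrected | 68.2% | 3.9% | 5.3% |
| Farrington-Manning, Miettinen-Nurminen, Newcombe | 63.7% | 4.4% | 4.98% |

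At 5.5% versus 0.5% failures the Wald rule's error is 10.3%.

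**Larger evaluable numbers.**

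- 114 per arm (no loss at all): Farrington-Manning and Newcombe 73.7% power; Wald 83.5% power with 6.8% error.
- 130 per arm: Farrington-Manning 80.0%, Newcombe 81.1%.

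**What this means for one result.** Take 97 per arm with 2 recurrences among the doctors' patients.

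- 2 among the CHOs' patients: Newcombe upper limit 4.2%, which passes.
- 3 among the CHOs' patients: the difference is 1/97 = 1.03% and the Wald limit is 0.0103 + 1.645 × √(0.000309 + 0.000208) = 4.8%, which passes. The Newcombe limit is 5.6%, which fails; Farrington-Manning also fails.

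With about two events expected per arm, this is a likely outcome, and the choice of interval alone decides it.

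**The case against.** **The arithmetic is right and the formula is conventional.** True: 97 follows from the stated inputs. The fault lies in the power and level claimed for it, because the formula is used where it does not apply.

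**The protocol never commits to a Wald limit, and naming the interval can be left to the SAP.** This stands in part. The 7.75% error arises only if a Wald limit is used, and the absence of a named interval is not the complaint. The power, level and sample size, however, are stated in the protocol, and no rule checked that holds its level reaches 80% at 97 per arm.

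**64% is the low end.** This has weight. Agresti-Caffo gives 71.3% and continuity-corrected Wald 68.2%, though both go slightly above 5% in places. Section 4 (Feasibility) reports over 95% one-year follow-up in a similar trial by collaborators. At 95% retention, 114 × 0.95 ≈ 108 are evaluable and score or Newcombe power is 69.3%; at 111 it is 74.0%. If true success were 99%, score power at 97 would be 79.6%. But the protocol plans for 15% loss and 98% success, and at 98% even complete follow-up leaves power at 73.7%.

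**Score-type limits are not perfect either.** At 130 per arm the worst-case error of Farrington-Manning and Newcombe is 5.15%. That is a small excess from discreteness, far from Wald's 13.1% worst case at 97, but it means 130 should be read as approximate.

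**One-sided 5% is inferred.** Correct, and the protocol should state it. A two-sided 5% level makes matters worse: score power at 97 per arm drops to 47%.

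**Conclusion.** The concern holds. On the protocol's own assumptions, 97 evaluable per arm does not give 80% power at a 5% level. With a limit that keeps its level the power is about 64%, so the chance of missing non-inferiority when the cadres are identical is about 36% rather than the stated 20%. With no losses that chance is still about 26%. If a Wald limit is used, power is about 81% but the false-claim rate is nearly 8% at 7% versus 2% failures, and higher when the doctors' failure rate is lower.

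This rests on a one-sided 5% level, a margin of 5 percentage points on the risk difference, 98% success in both arms, and independent patients. No allowance is made for clustering by operator; section 4.1 sets a minimum of five operators per cadre, and the effect of that is not quantified here.

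**What to change.** Keep the 228 patients. In the sample size paragraph of section 4.1:

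1. State that the 5% level is one-sided, if that is what was intended.
2. Name the limit for the risk difference: a score-type limit (Farrington-Manning or Miettinen-Nurminen) or Newcombe.
3. Replace the 80% claim with wording such as: *With a one-sided 5% level and a 5 percentage point margin, power is about 64% with 97 evaluable patients per arm and about 74% if all 114 per arm are evaluated, before allowing for clustering by operator.*

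The change should be made before outcome data are examined, because the interval can decide the result on a single recurrence. It costs one less favourable figure and one line of method wording. Restoring 80% instead would take about 130 evaluable per arm, which at 15% loss is 130 / 0.85 ≈ 153 per arm, or 306 in total. That is not required for this correction.
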